### Sample size and power

We present in Table 1 results from our *a priori* power analyses to evaluate the impact of the full implementation of Appy-CDS (Hy 2). Power estimates are based on 14 clinical sites. We anticipate 15 sites will be available, 8 intervention and 7 control sites. Over the 36-month study period, we anticipate 24,603 patients aged 5-20.9 will present with acute abdominal pain, of whom 2,634 (11%) will have appendicitis. Based on our previous work and review of other prediction rules, we anticipate that the Triage CDS will identify about 50% of patients who present to the ED with acute abdominal pain as being “at risk for appendicitis”. Thus, the

| Table 1. Power estimates*                                                                       |                     |     |
|-------------------------------------------------------------------------------------------------|---------------------|-----|
| Number of patients enrolled per ED per year                                                     | Decrease in imaging |     |
|                                                                                                 | 25%                 | 20% |
| 200                                                                                             | 80                  | 63  |
| 300                                                                                             | 91                  | 82  |
| 400                                                                                             | 98                  | 86  |
| *Assumptions: Number of sites: 14
Intra-class correlation = .05
Baseline CT Use Rate = .3 |                     |     |

total number of patients at risk for appendicitis, and whose outcomes we will evaluate across the 14 EDs, is forecasted to be 4,200 per year (or on average, 300 patients per ED). Based on preliminary data from the participating EDs, we estimate that the baseline utilization of CT is 30%. We anticipate that the group of ED-level covariates and the temporal correlation with the error structure will explain a significant proportion of variance of the dependent variable. However, power may be overestimated because sample sizes will vary by ED. Our power analyses consider a range for possible decreases in imaging rates and sample sizes while fixing a high intra-class correlation. Here, we report the estimated power to detect a significant period intervention effect, assuming a 2-tailed test with alpha set to 0.05. Actual power of our intervention may vary if enrollment goals are not reached.

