### 3) Study Sites and Population

We will conduct a prospective cluster-randomized clinical trial at 17 general EDs in two large care systems to evaluate the impact of Appy-CDS on CT and ultrasound use, health care outcomes, and direct medical expenditures. We will first measure ultrasound and CT use for 6 months pre-intervention in children identified at triage as at risk for appendicitis presenting for care in a participating ED. We will then group some sites with significant provider cross-coverage and pair within clusters by pediatric volume. We will then randomize half of the clusters to receive the full Appy-CDS. CT and ultrasound utilization in intervention and control sites will be measured for 24 months after the full Appy-CDS “go-live” date. Rates of perforation, negative appendectomies, and missed appendicitis will be monitored as safety outcomes. We will compare resource use and re-visit rates between intervention and control EDs within 7 days of the index ED visit. Figure 2 is an overview of the study design.

This study includes 17 general EDs operated by two health systems: HPMG (Regions, Hudson, Lakeview, Methodist, Westfield and Amery), in the Upper Midwest and KPNC (Sacramento, Roseville, South San Francisco, San Rafael, Santa Clara, South Sacramento, San Leandro, San Francisco, Fremont, Oakland and Richmond). These 17 EDs provide care to a diverse pediatric patient population (34% Hispanic, 19% African-American, and 11% Asian). None of the participating EDs are university-based; however, 5 EDs have academic affiliations. Most ED clinicians are board-eligible or board-certified emergency medicine physicians. Ultrasound is available at each participating ED, and 5 sites are referral centers for pediatric appendectomies. Each ED currently uses the EpiCare EHR (Verona, WI). Both health systems have agreed to participate and work with the study investigators to create linkages between their EHR and the Appy-CDS tool. Collectively, the 17 participating EDs have more than 650,000 annual ED visits, of which 101,014 are patients aged 5-20 years).

To be included, patients must: a) be 5-20.9 years old on the index date, and b) present to a participating ED with a chief complaint of acute abdominal pain.

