## Protection of Human Subjects

### a) Risks to Subjects

#### Human Subjects Involvement and Characteristics

Potentially eligible study subjects will include roughly 25,000 patients 5 to 20.9 years old who present to a participating ED with a chief complaint of acute abdominal pain over a 30-month period. We anticipate approximately 12,600 will have right sided or generalized abdominal pain for <5 days, and no other exclusion criteria, and thus be enrolled.

Study subjects also include roughly 414 clinicians at the two participating hospital systems (17 EDs). To participate in this study, ED clinicians must practice at one of the 17 EDs and be trained in emergency medicine, internal medicine, or family medicine or be a physician extender (nurse practitioner or physician assistant).

Limited clinical data from automated diagnostic, pharmacy, and laboratory databases will be collected for study subjects for specified periods of time to (a) identify eligibility for the study and the analysis based on age, presenting chief complaint, comorbid conditions, and responses to the Appy-CDS system and to (b) assess the impact of study interventions on implementation of Appy-CDS on use of CT and ultrasound and rates of perforated appendicitis, negative appendectomy, and missed appendicitis.

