**Table 7. Example Enrollment Table**

|                                                      | HP                         |                       | KP                         |                       |
|------------------------------------------------------|----------------------------|-----------------------|----------------------------|-----------------------|
|                                                      | Intervention
2 clusters | Control
2 clusters | Intervention
4 clusters | Control
4 clusters |
| Pre-Intervention period (n)                   | 204                 | 75             | 853                 | 767            |
| Per cluster (n)                               | 102                 | 38             | 213                 | 192            |
| Goal per cluster (n)                                 | 200                        | 200                   | 200                        | 200                   |
| Intervention period (n)                              | 114                        | 88                    | 317                        | 240                   |
| Projected annual                                     | 342                        | 264                   | 1268                       | 960                   |
| Projected over 2-year
intervention period | 684                 | 528            | 2536                | 1920           |
| Projected per cluster (n)                     | 342                 | 264            | 634                 | 480            |
| Goal per cluster                              | 400                 | 400            | 400                 | 400            |

Missed eligibles may occur at several stages. First, the Triage BPA may not fire due to changes in workflow and timing of nurse charting of chief complaint. Second, the Triage BPA may not be completed, thus eligibility cannot be confirmed. Third, patients with final diagnosis unavailable, perhaps due to transfer to an outside facility, cannot be captured.

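### Table 1's 91%/82% power rests on 14 sites, an enrolment forecast above the trial's own projection and no stated between-period correlation; restated for 12 clusters it is at best 81%/62% with a t reference (88%/71% normal)

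*Combined protocol and SAP*

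**What the plan says.** The section Sample size and power states: "Power estimates are based on 14 clinical sites". Table 1 assumes an ICC of 0.05, a baseline CT rate of 0.3 and a two-sided 5% test. For a 25%/20% decrease it gives 80/63, 91/82 and 98/86 at 200, 300 and 400 patients per ED per year. The forecast that selects the 300 row is that the at-risk population "whose outcomes we will evaluate across the 14 EDs, is forecasted to be 4,200 per year". The authors describe the calculation as varying effect and "sample sizes while fixing a high intra-class correlation".

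Other parts of the document give different numbers:
- The same section adds: "We anticipate 15 sites will be available, 8 intervention and 7 control sites".
- Section 3 says: "We will conduct a prospective cluster-randomized clinical trial at 17 general EDs in two large care systems". It then says: "We will then group some sites with significant provider cross-coverage and pair within clusters by pediatric volume", after which half of the clusters are randomised.
- Table 7 (section 9) lists 2+2 HealthPartners and 4+4 Kaiser clusters, with a goal of 400 per cluster over two years. Its row "Projected per cluster (n)" shows 342, 264, 634 and 480.
- The human-subjects section, for a 30-month period, says: "We anticipate approximately 12,600 will have right sided or generalized abdominal pain for <5 days".
- The pre-period is 6 months in section 3. In section 10 the triage tool runs for 12 months before randomisation.

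Under Hypotheses 2 and 3 the test is a time-by-treatment interaction (difference-in-differences). The power section mentions temporal correlation in general terms but gives no value.

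**The concern.** In a pre/post comparison of clusters, power depends on how well an ED's earlier CT rate predicts its later one, more than on the ICC itself. If the two are almost perfectly correlated, cluster effects cancel and the ICC hardly matters. If they are not, the uncancelled part remains in the variance however many patients each ED contributes. A power table that gives the ICC but not this correlation cannot be interpreted, and a high ICC is then little evidence of caution.

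The table also predates the current units of randomisation and sits beside a forecast that the trial's own enrolment table does not support. At stake is how a null result is read. A reader who trusts 91%/82% would take it as good evidence against a 20 to 25% reduction.

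**Working it through.** **Inputs.** Baseline p0 = 0.30; p1 = 0.225 or 0.24 (relative reductions); ICC ρ = 0.05; two-sided α = 0.05 (Table 1 and text). J = 7 clusters per arm (14 sites). Pre 6 months, post 24 months (section 3). The between-period cluster correlation r is not in the documents, so it is varied.

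**Formula.** With σ² = p0(1−p0) = 0.21 and the control rate flat:

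Var = (1−ρ)[σ²/(J·m_pre) + σ²/(J·m_post)] + (1−ρ)[σ²/(J·m_pre) + p1(1−p1)/(J·m_post)] + 2ρσ²(1−r)(2/J)

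Normal power = Φ(δ/√Var − 1.96).

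**Step 1: Table 1 at 300 per ED per year** (m_pre = 150, m_post = 600), r = 1.
- 25%: control 0.95 × (0.000200 + 0.000050) = 0.0002375; intervention 0.95 × (0.000200 + 0.0000415) = 0.0002294. Var = 0.000467, SE = 0.0216, 0.075/SE = 3.47, power 93.5%.
- 20%: Var = 0.000469, 0.06/SE = 2.77, power 79.1%.
- At r = 0.95 the last term adds 2 × 0.05 × 0.21 × 0.05 × 2/7 = 0.0003. Var becomes 0.000767 for the 25% effect and power falls to 77%.

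| 14 sites, normal test, 6/24 months | 200 | 300 | 400 |
|---|---|---|---|
| Table 1 as stated | 80/63 | 91/82 | 98/86 |
| r = 1 | 81/62 | 93/79 | 98/89 |
| r = 0.95 | 66/47 | 77/58 | 84/65 |
| r = 0.90 | 55/38 | 63/45 | 68/49 |
| r = 0.80 | 41/28 | 45/31 | 48/33 |

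The stated table is approached, not reproduced: the 300 row misses by 2 to 3 points and no variant tried matches every cell. A post-only comparison with ICC 0.05 gives only 29/20 at 300. The stated climb from 80 to 98 as enrolment doubles also points to r near 1, because at r = 0.80 it would be 41 to 48. With a 12-month pre-period, r = 1 overshoots (99.5/95 at 300) and the best fit is about 0.97.

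**Step 2: enrolment.**
- Table 7 post-period projection: 684 + 528 + 2,536 + 1,920 = 5,668 over two years, or 2,834 per year; 2,834/4,200 = 67%.
- Annualisation: 114 becomes 342 (×3) and 317 becomes 1,268 (×4), so these extrapolate about 4 and 3 months.
- Pre-period: 204 + 75 + 853 + 767 = 1,899. Total 1,899 + 5,668 = 7,567, or 60% of 12,600.
- 12,600 = 3 × 4,200 is 36 months of accrual, although the text attaches it to 30 months.

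**Step 3: current design.** Six clusters per arm. Table 7 sizes per cluster (pre, post): HP intervention 102, 342; HP control 37.5, 264; KP intervention 213.25, 634; KP control 191.75, 480. For each cluster v = (1−ρ)[σ²/m_pre + p(1−p)/m_post] + 2ρσ²(1−r), where p is the post-period rate in that arm. Each arm's variance is 1/Σ(1/v), and the two arms are added. At r = 1 the 25% effect has Var = 0.000565 and δ/SE = 3.15; the 20% effect has Var = 0.000568 and δ/SE = 2.52.

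| 12 clusters, Table 7 sizes | normal | t, 10 df |
|---|---|---|
| r = 1 | 88/71 | 81/62 |
| r = 0.95 | 68/49 | 59/42 |
| r = 0.90 | 54/38 | 46/32 |
| r = 0.80 | 38/26 | 32/22 |

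With equal weight per cluster, r = 1 and t give 68/50.

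**Step 4: what drives the loss** (r = 1, 4,200 per year held fixed). Moving from 14 sites to 12 clusters leaves normal power at 93.5/79.1 and moves t power from 88.9/72.1 to 87.8/70.5, so the cluster count alone costs at most 1 to 2 points. Using t instead of normal costs about 5 to 7 points with 14 sites, and Table 7 enrolment a further 7 to 8.

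**The case against.** The documents already cover part of this. Table 1 has a 200-per-ED row (80/63), and 2,834/14 = 202. Table 7's own goal is 200 per cluster per year, and its projection averages 5,668/12 = 472 per cluster over two years, above the goal of 400 (the HealthPartners clusters fall below it). The power section warns that unequal ED sizes may make power overestimated and that a shortfall in enrolment would change it. Table 7 is labelled an example and rests on a few months of data. All of this stands. But the warnings are unquantified and mention neither cluster count nor between-period correlation, and the 200 row covers lower enrolment only if that correlation is near 1.

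A reader might infer more than the documents support:
- *That Table 1 assumes zero between-period cluster variance.* No such assumption is stated. It is one reading of the numbers, it does not reproduce the 300 row, and with the 12-month pre-period the best fit is about 0.97.
- *That the loss comes from having 12 clusters instead of 14.* Step 4 shows otherwise.
- *That with drift, extra patients hardly help.* At r = 0.95, going from 200 to 400 per ED raises power from 66 to 84 (25% effect) and from 47 to 65 (20% effect).
- *That the trial has about even odds of detecting a 25% effect.* With t and Table 7 sizes that needs r of about 0.90, which is an assumption.
- *That the trial should be powered for the pilot effect.* The pilot used a simpler order-time alert in children's hospital EDs; a row for it is optional.

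**Conclusion.** The concern holds in a limited form. The 91%/82% figure belongs to 14 sites and 4,200 patients per year, and is approached only with a between-period correlation near 1 that the plan never states. Describing the ICC as high therefore gives little of the conservatism it suggests. For 12 clusters at Table 7 sizes with precision weighting, power at correlation 1 is 81/62 (t, 10 df) or 88/71 (normal). The 25% effect stays above 80% in that best case, while the 20% effect does not under either reference. Below correlation 1 both fall, to 59/42 at 0.95 and 46/32 at 0.90 with t.

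These results rest on Table 7's early projections and pre-period counts taken as they stand, on a flat control rate, and on a correlation shown as a range because the documents give none.

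**What to change.** Restate Table 1 for the 12 randomised clusters, using current projected sizes with their inequality, a t reference with cluster degrees of freedom, and an explicit between-period correlation. Estimate that correlation from pre-intervention or historical CT rates by ED, and show results over about 0.8 to 1.0. Report the resulting power or the minimum detectable reduction. Update the 4,200-per-year and 12,600 forecasts, with the accrual period each refers to, and align the 14, 15 and 17 site counts with the clusters. Reconcile the 6- and 12-month pre-periods, since the answer depends on which is used.

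The cost is one table, a few sentences and a short analysis of existing data. No extra enrolment is needed; the stated power becomes less favourable.

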### Missing data

Missing data on predictors of appendicitis and use of diagnostic imaging in patients identified at risk of appendicitis will be handled using multiple imputation techniques applying a regression switching with predictive mean matching (MICE-PMM). Patient characteristics, implementation variables, and provider characteristics will be used to maximize information used for multiple imputations.

## b) Measurement of Outcomes

Progress of all eligible patients before and during implementation will be followed for all outcomes.

### Identification of a cohort of patients with acute abdominal pain at risk for appendicitis (Hypothesis 1):

Using existing EHR data and simple prompts implemented at triage at all 17 sites over the 6-month pre-intervention period and 24-month trial we will identify our study cohort of children and adolescents at elevated risk for appendicitis. The algorithm underlying this tool will exclude patients with chronic abdominal pain, abdominal trauma, and/or pregnancy, because their management is beyond the scope of the proposed intervention. For patients undergoing an appendectomy within 7 days of their index ED visit, a trained, blinded nurse abstractor will review their pathology report. For patients undergoing appendectomy, appendicitis is defined by specific terminology on the pathology report, as in our previous multicenter study (consistent with appendicitis, neutrophil invasion of tissue, serosal inflammation, acute peri-appendicitis, or acute appendicitis). For patients with perforation undergoing drainage and/or intravenous antibiotics and interval appendectomy, diagnosis will be based on clinical notes from the treating surgeon. For patients transferred from the ED where they initially sought care to a facility with pediatric surgical expertise, we will seek final diagnoses and pathology reports from the receiving institution. If we are unable to verify final diagnosis, the patient will be excluded from primary analyses. These patients may be included sensitivity analyses with the diagnosis of appendicitis or not appendicitis assigned based on provider impression and imaging available at the time of ED discharge / transfer. For HPMG, outside of the study EDs, Children's Hospital would be the primary outside institution to receive transfers for further evaluation and appendectomy. Thus, we will establish a registry of patients with a discharge diagnosis of appendicitis from Children's Hospital and use a probabilistic method to determine whether these patients are matches with patients receiving care in the HPMG study EDs. KPNC uses a hub and spoke system for pediatric surgery. Among the 11 CREST sites are four pediatric surgical hubs.

**Reduction in CT use** (Hypothesis 2): Among pediatric patients identified through the Appy-CDS as at risk for appendicitis, receipt of an abdominal and/or pelvic CT during the index ED visit will be determined through completed orders in Epic. We will identify CTs obtained using the following CPT codes: 74150, 74160, 74170, 74174, 74176, 74177, 72192, 72193, and 72194. Only CTs ordered in the ED will be included.

**Total Imaging Utilization** (Hypothesis 3): Among pediatric patients identified through the Appy-CDS as at risk for appendicitis, receipt of an abdominal and/or pelvic CT or abdominal and/or pelvic ultrasound during the index ED visit will be determined through completed orders in Epic. We will identify CTs as described above and ultrasounds using the following CPT codes: 76705, 76700, 76770, 76775, 76857, 76830, and 76856. Only ultrasounds ordered in the ED will be included.

**Direct medical expenditures** (Hypothesis 4): For HP and KPNC members, utilization of all medical services within 7 days of the index ED visit will be captured from insurance claims data. Hospital-based costs at the study sites for nonmembers will be assessed using Total Care Relative Resource Value units (TCRRVs), described in detail below. While the goals of the CDS are to reduce CT use, the CDS may inadvertently lead to overuse of other diagnostic tests. In addition, by discouraging CT, the CDS may result in prolonged ED or inpatient observation. To capture all potential costs related to the treatment episode, we will include all utilization of health care services occurring at the ED visit and during the subsequent 7 days. This time window is adequate to include the most common complications associated with an appendiceal perforation. Across both participating health systems, coding guidelines and incentives ensure that all services provided should be accurate in the claims data. Although we do not anticipate differences in appendectomy or adverse event rates related to initiation of the Appy-CDS, if this does occur, we will assess the potential long- term impact of these differences by modeling long-term impact over a 12- and 24-month timeframe.

**Appendiceal perforation, negative appendectomies, and missed appendicitis** (safety outcomes): Although it is unlikely that the Appy-CDS will significantly increase rates of adverse events, the following clinical or safety outcomes will be monitored both before and during the full Appy-CDS intervention. *Appendiceal perforation* will be evaluated in patients who undergo appendectomy based on chart review of the surgeon's intra-operative note. As in our previous work, perforation will be defined by keywords in the operative report (presence of abscess, peritonitis, complex appendicitis, or purulent material). In addition, we will review all charts for patients with a discharge diagnosis of perforated appendicitis (ICD-9 540.1) who do not undergo an appendectomy during their index hospitalization, because a subset of patients with appendiceal perforation (4% in our previous multicenter cohort, unpublished data) will be admitted for intravenous antibiotics and undergo an interval appendectomy 6-12 months later. *Negative appendectomies* are appendectomies in which the pathology report reveals no evidence of appendiceal inflammation. This will be determined via review of pathology reports. *Missed appendicitis* is when a patient presents for the evaluation of abdominal pain, is discharged home, and returns within 1 week with appendicitis. Missed appendicitis will be identified through review of automated EHR data for all patients with appendicitis. As described above, under exclusion criteria, patients who are transferred for definitive care and whose final pathology and surgical reports are not available will not be included in the assessment of safety outcomes.

